## Abstract

**Background:** Coronary artery disease is a leading cause of morbidity and mortality in Saudi Arabia. No national mechanism exists for standardized CABG outcome surveillance. The Saudi CABG Audit and Registry (SCAR) was established to address this gap. **Methods:** SCAR is a prospective multicenter clinical quality registry enrolling consecutive patients undergoing isolated or combined CABG across Saudi Arabia. The dataset captures more than 100 variables spanning demographics, comorbidities, operative details, in-hospital outcomes, and longitudinal follow-up to one year. Primary outcomes include in-hospital mortality, 30-day major adverse cardiac and cerebrovascular events (MACCE), deep sternal wound infection, and unplanned reoperation. **Results:** The registry incorporates structured follow-up at 30 days, 3 months, 6 months, and one year, governed through three national committees overseeing data quality and dissemination. A four-tier analytical framework progresses from descriptive analyses through risk-adjusted benchmarking, validation of international risk models, and future development of a locally derived risk prediction model. Implementation commences with a pilot phase enrolling 100–150 consecutive procedures across four centers over three months. **Conclusions:** SCAR represents the first dedicated national CABG registry in Saudi Arabia. Through risk-adjusted benchmarking and structured feedback, the registry may support quality improvement, multicenter research, healthcare planning, and development of locally relevant risk stratification tools.

## 1. Background

Cardiovascular disease remains the leading cause of mortality worldwide, accounting for an estimated 17.9 million deaths annually [1]. In Saudi Arabia, the burden continues to rise because of the high prevalence of obesity, diabetes mellitus, hypertension, dyslipidemia, and sedentary lifestyles [2,3]. Coronary artery disease remains the most common manifestation of cardiovascular disease and is a major contributor to morbidity, mortality, and healthcare expenditure within the Kingdom. Coronary artery bypass grafting (CABG) remains a cornerstone revascularization strategy for patients with complex multivessel disease, diabetes mellitus, and impaired ventricular function. Despite advances in medical therapy and percutaneous coronary intervention, CABG continues to provide substantial survival and symptomatic benefits in appropriately selected patients with advanced coronary artery disease.

Advances in cardiac surgery, anesthesia, and perioperative care have substantially improved CABG outcomes over recent decades. However, accurate evaluation of surgical performance and patient outcomes requires comprehensive, standardized, longitudinal data collection systems capable of capturing perioperative variables, postoperative complications, and long-term outcomes [4]. To address this need, several countries have established national cardiac surgery registries, including the Society of Thoracic Surgeons (STS) Adult Cardiac Surgery Database in the United States, the European E-CABG Registry, and the National Adult Cardiac Surgery Audit (NACSA) in the United Kingdom [5,6,7]. These registries have supported risk-adjusted benchmarking, quality improvement initiatives, public reporting, and development of evidence-based clinical guidelines. For example, participation in the STS database has been associated with reductions in operative mortality following isolated CABG from approximately 2.5% to approximately 1.9% in recent years [5]. These registries have demonstrated the value of structured clinical data collection in identifying practice variation, supporting quality assurance, and informing healthcare policy.

## 2. Rationale

Despite the high burden of coronary artery disease and the widespread performance of CABG procedures across tertiary cardiac centers in Saudi Arabia, there is currently no national cardiac surgery registry capable of systematically capturing perioperative and long-term outcomes. Existing data are largely limited to isolated single-center experiences, restricting opportunities for national benchmarking, validation of international risk prediction models, development of locally relevant risk stratification tools, and data-driven healthcare planning. Although initiatives such as the SPACE registry have demonstrated the feasibility of large-scale cardiovascular data collection within Saudi Arabia [8], no equivalent national framework currently exists for surgical coronary revascularization.

The Saudi CABG Audit and Registry (SCAR) was therefore developed as a prospective multicenter clinical quality registry for patients undergoing CABG surgery across Saudi Arabia. The registry incorporates internationally validated parameters and definitions, including EuroSCORE II [9], SYNTAX score [10], Kidney Disease: Improving Global Outcomes (KDIGO) criteria [11], and standardized complication definitions, while also integrating locally relevant domains such as frailty, cardiac rehabilitation, healthcare access, and patient-reported outcomes. The dataset incorporates key echocardiographic and cardiovascular imaging parameters used in contemporary perioperative risk assessment, reflecting the established and growing role of multimodality imaging in cardiovascular risk stratification and outcome prediction [12]. Validated quality-of-life instruments, including the EuroQol Five-Dimension Five-Level questionnaire (EQ-5D) and the Short Form 36 Health Survey (SF-36), together with return-to-work and functional recovery measures, are incorporated to support patient-centered outcome assessment. In addition, referral to and participation in cardiac rehabilitation programs will be captured because of their established association with improved functional recovery and long-term cardiovascular outcomes.

Through standardized national data collection, structured audit mechanisms, risk-adjusted benchmarking, and institutional feedback, SCAR may support quality improvement initiatives, multicenter cardiovascular research, and evidence-informed healthcare planning. The registry is also intended to provide a foundation for future expansion into other cardiac surgical procedures and facilitate Saudi Arabia’s participation in international cardiovascular surgical collaborations. This study is registered in ClinicalTrials.gov with the identifier NCT07316777.

## 3. Study Design

SCAR is a prospective, observational, multicenter clinical quality registry designed to capture detailed perioperative and long-term outcome data for patients undergoing CABG in Saudi Arabia. The registry is intended to support risk-adjusted benchmarking, quality improvement initiatives, and the generation of real-world evidence to inform clinical practice, national cardiac surgery policy, and multicenter research. Its primary objectives are to systematically document patient characteristics, operative strategies, and short- and long-term outcomes while facilitating national performance monitoring and audit activities.

## 4. Current Implementation Status

At the time of manuscript submission, SCAR remains in the preparatory implementation phase. Four tertiary cardiac surgery centers are currently under review for pilot participation, with institutional collaboration agreements progressing through local institutional review board (IRB) review and site onboarding processes at each prospective center. The names of participating institutions will be confirmed and disclosed following completion of local IRB review and formal execution of collaboration agreements. Patient recruitment and data collection have not yet commenced.

## 5. Pilot Phase

Registry implementation will commence through an initial pilot phase involving four selected tertiary cardiac surgery centers. The pilot phase is expected to enroll approximately 100–150 consecutive CABG procedures over a period of three months and is intended to evaluate operational feasibility, data completeness, follow-up capture rates, data quality processes, user experience, and platform performance before broader national implementation.

Key pilot success indicators will include a data completeness rate of at least 90% across mandatory fields, a 30-day follow-up capture rate of at least 80%, adherence to standardized variable definitions, usability of the electronic platform, and overall operational feasibility. Predefined thresholds for these indicators must be met before progression to national rollout is initiated. National expansion is anticipated to begin within 12 to 18 months of pilot phase completion, with the registry aiming to capture a substantial and progressively increasing proportion of CABG procedures performed at tertiary cardiac surgery centers across Saudi Arabia. Findings from the pilot phase will be used to refine registry procedures and inform the timeline and scope of subsequent national expansion.

## 6. Study Population

Patients undergoing coronary artery bypass grafting (CABG) will be enrolled consecutively from participating tertiary cardiac surgery centers across Saudi Arabia.

### 6.1. Inclusion Criteria

Age ≥ 18 years.Patients undergoing isolated CABG.Patients undergoing CABG combined with concomitant cardiac procedures (e.g., valve repair or replacement).Procedures performed using on-pump or off-pump techniques.Elective, urgent, or emergent procedures.Open, minimally invasive, or robotic-assisted surgical approaches.

### 6.2. Exclusion Criteria

Patients aged < 18 years.Redo CABG procedures in which the primary operative record is unavailable or irretrievable.

For the purposes of this registry, a primary operative record will be considered unavailable or irretrievable if the original operative documentation and essential perioperative data required for baseline characterization and risk adjustment cannot be obtained from institutional records despite reasonable retrieval attempts.

Participation in the registry will not influence clinical decision-making, perioperative management, or therapeutic strategies, which will remain entirely at the discretion of the treating clinical team according to institutional practices and current clinical guidelines.

All eligible CABG procedures will be entered consecutively to maximize representativeness and minimize selection bias. Participating centers will be encouraged to maintain screening logs documenting all eligible procedures and reasons for non-enrollment where applicable, thereby supporting assessment of case capture rates and registry representativeness. Where local consent requirements result in patient non-participation, this will be recorded in the screening log to allow evaluation of any systematic differences between enrolled and non-enrolled cases. Isolated CABG and combined CABG procedures will be analyzed separately where appropriate, with procedure type incorporated into risk-adjustment models and benchmarking analyses.

Informed consent procedures will follow the policies and requirements of participating institutions and reviewing ethics committees. Participating centers will utilize their own locally approved consent forms and consent procedures where required by institutional policies or ethics committees. Where written informed consent is required, patients will be provided with information regarding the purpose of the registry, the nature of the collected data, confidentiality safeguards, and their rights regarding participation and withdrawal. Variability in local consent requirements across participating institutions may influence patient enrollment procedures and could potentially affect case capture rates and registry representativeness; this is acknowledged as a limitation of the multicenter design. Registry participation will not affect clinical care or treatment decisions.

## 7. Registry Design

The Saudi CABG Audit and Registry (SCAR) is a national clinical quality registry designed to systematically capture perioperative and long-term outcomes of patients undergoing coronary artery bypass grafting (CABG) across Saudi Arabia. The registry was developed by adapting key structural and operational principles from leading international cardiac surgery registries while incorporating locally relevant clinical and healthcare system considerations. SCAR aims to establish a standardized national platform for outcome monitoring, benchmarking, quality improvement, and multicenter cardiovascular research.

The registry is being developed through a multidisciplinary collaborative framework involving cardiac surgeons, senior residents, data scientists, epidemiologists, health informatics specialists, and health services researchers. This working group has overseen registry design, parameter selection, variable standardization, platform development, and quality assurance processes. SCAR will operate through a fully digital infrastructure with centralized governance to ensure consistency, data integrity, and standardized reporting across participating centers.

Registry variables, definitions, and data collection procedures will undergo periodic review to ensure continued relevance and alignment with evolving evidence, clinical practice, and stakeholder requirements.

## 8. Governance Structure

The registry will operate under a structured national governance framework designed to ensure scientific integrity, operational efficiency, data quality, and collaborative participation across participating institutions. Oversight of the registry will be conducted through three principal committees: the Steering Committee (SC), the Working Committee (WC), and the Publication and Dissemination Committee (P&DC), as illustrated in Figure 1.

Members of the committees will be nominated by their respective institutions and appointed for renewable one-year terms. Collectively, the committees will oversee protocol adherence, registry operations, institutional coordination, data quality assurance, dissemination activities, implementation of registry policies, and strategic development of the registry.

## 9. Data Access and Use

All participating institutions will enter into formal data-sharing and collaboration agreements outlining governance principles, data confidentiality requirements, publication policies, and procedures for data access and use. Proposals for secondary analyses or sub-studies utilizing SCAR data will undergo committee review and approval based on scientific merit, methodological rigor, feasibility, and alignment with registry objectives.

## 10. Quality Assurance and Oversight

Data quality will be supported through standardized variable definitions, mandatory data fields, electronic validation rules, user training programs, periodic data quality assessments, and source-data verification audits. Participating centers will receive regular feedback regarding data completeness, consistency, follow-up performance, and outcome reporting. Centers demonstrating persistent data quality concerns may undergo targeted retraining, corrective action procedures, and follow-up quality reviews.

Source-data verification audits will be conducted on a random sample of 5–10% of submitted cases at each participating center per audit cycle to assess data completeness, accuracy, and consistency between registry entries and source clinical documentation. A missing data rate exceeding 10% across mandatory fields, or a pattern of systematic inconsistency identified during an audit, will trigger a formal corrective action process comprising targeted retraining, data reconciliation, and a follow-up quality review within 60 days. Data quality indicators, including completeness rates, follow-up capture rates, missing-data frequencies, and validation-error rates, will be monitored periodically by the registry governance structure.

As SCAR is an observational clinical quality registry without interventional components, the Steering Committee will assume responsibility for registry governance, data integrity, and quality assurance oversight during the pilot phase, fulfilling the functions typically discharged by a dedicated Data and Safety Monitoring Board. As the registry transitions to national rollout and the Steering Committee expands to include representatives from additional participating institutions, a formal independent oversight body will be appointed at the appropriate stage of registry maturation. Any significant concerns relating to data quality, governance, or registry operations will be reviewed through the registry’s governance framework and managed according to established quality assurance procedures.

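### Applied to the pilot, the 5–10% source-data audit verifies about 1–4 records per center, too few to judge accuracy or definition adherence by center or by variable

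*Protocol article*

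**What the plan says.** Section 10 of the protocol article sets the size of the source-data audit: "Source-data verification audits will be conducted on a random sample of 5–10% of submitted cases at each participating center per audit cycle". The purpose is "to assess data completeness, accuracy, and consistency between registry entries and source clinical documentation". Section 14 repeats the rule, and the Figure 2 caption and Table 2 repeat the percentage. None of these places gives a minimum number of records or a different fraction for the pilot.

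Section 10 also attaches a consequence to the audit. Either more than 10% missing data in mandatory fields, or a systematic pattern of discrepancies found at audit, starts formal corrective action at the center.

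Section 5 describes an "initial pilot phase involving four selected tertiary cardiac surgery centers", "expected to enroll approximately 100–150 consecutive CABG procedures over a period of three months". The pilot is "intended to evaluate operational feasibility, data completeness, follow-up capture rates, data quality processes, user experience, and platform performance". Its success indicators are at least 90% completeness, at least 80% capture of 30-day follow-up, and "adherence to standardized variable definitions, usability of the electronic platform, and overall operational feasibility". Thresholds on these indicators have to be met before national rollout begins.

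**The concern.** A percentage rule suits a large registry, where 5–10% of a center's cases is a workable sample. In a three-month pilot the same percentage leaves a handful of records. Source-data verification is nevertheless the only check in the article that compares an entry with the chart. The range checks, validation scripts and mandatory-field prompts in section 14 cover every case, but they find missing, implausible or inconsistent entries. They cannot tell that a plausible entry, such as no stroke or no deep sternal wound infection, departs from the source or the definition. The completeness indicator does not help either, because a field that is filled but wrong counts as complete.

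Adherence to definitions belongs to each variable and to each center's coding practice. If the pilot cannot look at that level, an outcome definition misapplied in part of one center's records could pass unseen into the national phase and into the benchmarking of section 15.

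**Working it through.** The article prints no number of audited records, so there is no figure of its own to reproduce.

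**Inputs.** From section 5: 100–150 procedures and 4 centers. From sections 10 and 14: 5–10% of cases per center per cycle. From the abstract: more than 100 variables per record. Assumed: an equal split across centers, the error rates used below, and the within-record correlation in step 5.

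**1. Records verified.** Cases per center: 100/4 = 25 and 150/4 = 37.5.

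| Cases per center | 5% | 10% |
|---|---|---|
| 25 | 1.25 | 2.5 |
| 37.5 | 1.875 | 3.75 |

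That is about 1–4 records per center. The whole pilot gives 100 × 0.05 = 5 to 150 × 0.10 = 15 records, or 8 to 16 if every center is rounded up. An unequal split leaves the smaller centers with fewer. Further cycles add nothing if each samples 5–10% of its own new cases.

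**2. What a clean audit excludes at one center.** With no error in n records, the one-sided 95% upper bound on the share of wrong records for a given variable is 1 − 0.05^(1/n) (binomial). This is 95% for n = 1, 78% for n = 2, 63% for n = 3 and 53% for n = 4.

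**3. Chance of meeting errors at one center.** Hypergeometric sampling without replacement from N = 25 or N = 37 cases. The scenario of about 20% uses 5 of 25 and 7 of 37 wrong records. The scenario of about 10% uses 2 of 25 (8%) and 4 of 37 (10.8%).

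| Records audited | About 20% wrong: at least one | About 20% wrong: at least two | About 10% wrong: at least one | About 10% wrong: at least two |
|---|---|---|---|---|
| 1 | 19–20% | 0% | 8–11% | 0% |
| 2 | 35–37% | 3% | 16–21% | 0.3–1% |
| 4 | 59–62% | 16–17% | 30–38% | 2–5% |
| 10 | 91–94% | 63–69% | 65–73% | 15–29% |

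Four records arise only at the upper end of pilot volume with a 10% sample (3.75 rounded up). With 25 cases the rule gives at most three. A pattern needs at least two discrepant records, so the columns for two or more are the ones that bear on the corrective-action trigger.

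**4. Pooled over the pilot, one variable.** With 5–15 records, the binomial chance of at least one error is 1 − 0.8^5 = 67% to 1 − 0.8^15 = 96% at a 20% error rate, and 41% to 79% at 10%. With no error found, the upper bound is 45% to 18%.

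**5. Pooled over the pilot, all fields.** Taking 100 fields per record, 5–15 records give 500–1,500 fields. The 95% half-width for a 5% discrepancy rate is 1.96 × √(0.05 × 0.95 × D / m), where m is the number of fields and D = 1 + 99 × ICC. It is 1.1–1.9 points at ICC 0 and 3.6–6.3 points at ICC 0.10. An overall rate can therefore be estimated to within a few points.

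**6. What precise estimation would need.** About 35 records estimate 90% agreement on one variable to ±10 points (1.96² × 0.9 × 0.1 / 0.1² = 34.6). Twenty-nine clean records bring the upper bound down to 10%. Per center, either number is close to the whole pilot volume or above it.

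**The case against.** A reader might infer that the pilot cannot assess data accuracy at all, that the rollout decision rests on this audit, or that the audit would pass nearly any center. The article supports none of these.

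- **Accuracy.** It is a purpose of the audit program, not a named pilot indicator. What section 5 names is the data quality processes, and a small audit can test whether the process works. Step 5 shows that a pooled field-level rate remains usable.
- **Rollout.** The decision also depends on completeness, follow-up capture, usability and feasibility. Nothing says that definition adherence is judged by the audit alone. The decision is for the registry as a whole, where the pooled chances in step 4 are better than the per-center ones.
- **Passing nearly any center.** A 59–62% chance of meeting an error with four records does not fit that description. A definition misunderstood across a center would affect most records. If 80% were wrong, one record would meet an error with 80% probability and two records with 96%.

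It can also be said that audit detail commonly sits in a fuller document, and that a percentage rule is neither contradictory nor wrongly stated. That is fair as to rounding, cycle length and the threshold for definition adherence, none of which is criticized here. The fraction and the pilot size are both stated, however, and the consequence follows from them.

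Finally, ten records per center is a modest number. It detects errors but does not measure a rate. At a 10% error rate it meets two or more errors only 15–29% of the time. This stands and limits what the fix can promise.

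**Conclusion.** The point holds at the level of center and variable. The stated rule applied to the stated pilot yields about 1–4 verified records per center and 5–15 overall. One record cannot show a pattern, and two to four records rarely do unless the error affects most of a center's cases. A clean result at one center leaves an error rate of 53–95% on any one variable unexcluded. Because source-data verification is the only described comparison with the chart, and definition adherence is among the indicators for rollout, the audit size should be settled before the pilot starts.

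The point does not extend to the pooled discrepancy rate, to completeness or follow-up capture, or to the audit percentage in the national phase. It rests on an equal split across centers, on audit cycles that do not resample earlier cases, and on illustrative error rates of about 10% and 20% that the article does not give.

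**What to change.** For the pilot only, state in sections 5, 10 and 14 that at least 10 randomly chosen records per center, or 5–10% of submitted cases if that is more, are verified in one audit completed before the rollout decision. In section 5, add that agreement with source on the primary outcome fields is reported pooled and per center as part of the definition-adherence indicator.

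The cost is 4 × 10 = 40 verified records in place of 5–15, so 25–35 more, by the same auditors. Section 4 says that recruitment has not begun, so the change can be made in time. The floor should not be carried over to every center and cycle: at 5% it would bind up to 10/0.05 = 200 cases per cycle.

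If 20% of a center's records are wrong, ten records give a 91–94% chance of meeting at least one error and 63–69% of meeting two or more. Per-center agreement from ten records should be read as a screen for common or systematic errors, not as a precise error rate. The pooled 40 records exceed the roughly 35 needed for ±10 points at 90% agreement on one variable, treating them as a simple random sample.
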